#### Inclusion criteria

2.5.2.

age of 18 years to 70 years;body weight stable (± 3%) for at least 3 months prior to study commencement;BMI (1) between 18.5 and 24.9 (± 0.5) kg/m^2^ or (2) between 30 and 50 kg/m^2^ (± 0.5) kg/m^2^ or waist circumference > 88 cm or > 102 cm for females and males, respectively;See Table 1 for specific group allocation criteria based on glucose, HbA1c, HDL-C, and triglycerides.

#### Exclusion criteria

2.5.3.

current or recent history cardiovascular diseases or events (e.g., ischemic, rheumatic, or congenital heart disease, stroke, peripheral vascular disease, heart failure, familial hypercholesterolemia or other monogenic dyslipidemia), use of cardiac implantable electronic devices;current or recent cancer, including remission, during the last 5 years;diseases known to affect the immune system, such as infectious, inflammatory, and autoimmune diseases or autoimmune-related or suspected conditions (e.g., T1D, systemic lupus erythematosus, inflammatory bowel disease), except for psoriasis, atopic dermatitis, and rheumatoid arthritis. Continuous use of anti-inflammatory or immunosuppressant drugs and supplements for which washout is not possible, except for medications which participants with obesity could not refrain from (e.g., baby aspirins);renal disorders, endocrine disorders other than T2D (e.g., acromegaly, Addison’s disease, Cushing’s disease);untreated or uncontrolled thyroid diseases (e.g., Hashimoto’s disease, hypothyroidism, hyperthyroidism);known allergy, aversion to any components of the menu, or restricted dietary patterns (e.g., gluten-free diet, vegetarianism, kosher or halal diets) for which accommodations within the menu are not possible;participants under titration of their medication or initiating a new treatment or HbA1c >10.5%women who are pregnant or plan to become pregnant during the study duration, who are lactating, who have an irregular menstrual cycle or are in perimenopause;regular recreational use of cannabis;taking part in any other intervention study that might affect the outcomes of the current study.

#### Enrolment

2.5.4.

Potential participants will complete a pre-screening and screening visit before entering the study. The pre-screening consists of a structured questionnaire, which can be completed online or through the telephone (Supplementary File 2). All pre-screening data is stored on the web-based software Research Electronic Data Capture (REDCap) (67). The study coordinator follows up with interested individuals by email and/or telephone to schedule their screening visit or let them know in case they are not eligible. At the screening visit, a trained research staff member (e.g., research coordinator, graduate students, investigators) will obtain written consent from interested individuals to confirm their eligibility by checking every inclusion and exclusion criteria. This visit includes blood tests, anthropometric measurements, and the completion of questionnaires regarding demographics, health, use of medications, and physical activity. During or after the screening visit, participants will not be enrolled in the study if they decline to participate after knowing more study details or if they violate any inclusion criteria. The enrollment period might generally vary from 3 days to 5 weeks depending on the necessity of a washout before study commencement or the availability of participants. The schedule of study visits and procedures are depicted in Figure 2.

**Figure 2 fig2:**
[figure not shown]
Schedule of enrolment, interventions, and assessments (SPIRIT figure).

### Withdrawal of participants

2.6.

Participants may be withdrawn from the trial either at their own request or at the discretion of the principal investigator if not compliant with the menu. Participants will be made aware via the information sheet and consent form that data collected up to the withdrawal date may still be used in the final analysis. If participants have consumed the control diet for at least 2 weeks, they will be asked if they would like to provide a blood sample before withdrawal. The reason for and date of withdrawal will be recorded on an electronic spreadsheet.

### Intervention

2.7.

#### Concomitant care and pre intervention requirements

2.7.1.

The administration of vaccines, application of botulinum toxin, use of antibiotics, supplements or other natural products, and blood donation is not permitted throughout the intervention and a four-week washout is necessary prior to study commencement. For recent surgical procedures, approximately 4 months or less, inclusion will be at the discretion of the principal investigator depending on the magnitude of the procedure. Participants should continue to take their regular medications [e.g., antilipemic (fenofibrate and atorvastatin), blood pressure-lowering (amlodipine, enalapril), antidepressants (escitalopram, bupropion, and amitriptyline), and glucose-lowering (metformin, insulin)]. Participants will be asked to refrain from performing vigorous physical activity, taking anti-inflammatory medications, and drinking alcohol 3 days prior to baseline study visits.

#### Standardized diet

2.7.2.

Participants will all consume an isocaloric standardized North American type diet for 4  weeks. All meals will be provided to participants for an optimal control of energy and nutrient intake. A seven-day cyclic menu was designed using The Food Processor Nutrition Analysis Software (v.11.0.3, ESHA Research, Salem, OR, 2015) to reflect as closely as possible current macronutrient intake averages in North America (68–70) with approximately 35% of energy as fat, 12.5% as SFA, 13% as monounsaturated fatty acids, 6% as PUFA, 48% energy as carbohydrates with a significant proportion of these coming from foods containing refined sugars, and 17% as proteins mostly from meat, meat products and dairy products. The breakfast meal represents approximately 20% of the daily energy intake whereas the lunch and dinner meals each provides 40% of daily energy intake (Supplementary File 3). Participants will be instructed to consume their meals entirely but will have the opportunity to spread out their food throughout the day. Participants will have free access to water and other non-caloric beverages during the feeding period according to their habitual consumption (or nearly calorie-free drinks, i.e., black coffee or tea). Adaptations will be made for participants with lactose intolerance, including the use of lactose-free milk, lactase, or fortified vegetable beverage (soy or rice), and for individuals with an aversion to vegetables or other meals of the menu when an adequate substitute based on nutrient composition can be provided.

#### Estimate of energy requirements

2.7.3.

Total energy expenditure of participants will be estimated using the Mifflin St. Jeor equation and metabolic equivalents (MET) to estimate physical activity level using a template spreadsheet by Gerrior et al. (71). If the desired MET was not available in the spreadsheet, they were inserted according to the 2011 Compendium of Physical Activities (72). Energy intake will then be prescribed for each participant according to their individual estimate of total energy expenditure. The energy content of the diet will be revised weekly according to body weight fluctuations throughout the intervention period. If body weight has a significant slope (i.e., increasing or decreasing) at a rate that yields a change ≥3% during the first 2 weeks, adjustments to the energy content of the diet will be made to offset changes in body weight and keep it constant for the remaining of the study period. Participants will be instructed to maintain their usual physical activity level throughout the intervention period except for the 3 days preceding blood sampling, during which they will be asked to refrain from intense physical exercise.

#### Food preparation and delivery

2.7.4.

All menu items (Supplementary File 4) will be prepared and portioned at the metabolic kitchen of the HNRU in accordance with the food safety standards and guidelines set by the Alberta Health Services. All food handlers have received training on food safety. Meals are prepared weekly and in batches. Batch cooking will be used to optimize weekly meal preparation and delivery to participants. Samples (200 g) of food cooked in batches will be saved and frozen up to 3 months after the last batch is consumed in case food safety analysis is needed. Preparation of high-risk foods (e.g., containing eggs or meat) will be temperature-controlled and recorded in a form. Meals will be prepared from Monday to Thursday and batch cooked meals are thawed overnight at 4°C on the day before portioning (Sunday–Wednesday). Meals will be placed into reusable ready to eat containers that are microwavable and dishwasher safe, sealable plastic bags, or disposable containers. All menu items are labeled, packed into reusable thermal bags, and maintained at 4°C until pick-up time. Food will be individually delivered by a trained study staff, including graduate students or other faculty members of the study team. Participants will come to the research unit to pick up their food every other day and on Friday they receive meals for Saturday, Sunday, and Monday. Participants will be instructed and will sign an agreement to store their food at 4°C within one-hour time frame and to properly re-heat it before consumption. Reusable items will be sanitized using a 200 ppm chlorine solution prepared daily (i.e., thermal bag and ice packs) or at 82^o^ C using a commercial dishwasher (Moyer Diebel Ltd. 501HT-70, Winston Salem, NC, United States) (i.e., food containers).

### Follow-up and extra visits

2.8.

Participants will be followed up to three times a week during their food-pick up. This visit takes approximately 10 min and includes body weight measurement, follow-up regarding compliance, scheduling of next visits, delivery of thermal bag containing meals and frozen reusable ice packs, and collection of reusable items (i.e., empty containers and ice packs) from participants. Additional site monitoring visits may be scheduled in case participants require additional assistance from the study team to complete the food frequency questionnaire FFQ, which is used to assess habitual dietary intake. Participants will be able to discuss any aspect of the study with the trial manager, including their blood tests, body composition, and dietary assessment results. To help retain participants on the study, they will receive emails or phone calls to support them throughout the duration of the study and will be reminded about their scheduled visits.

### Data collection

2.9.

#### Compliance

2.9.1.

The participant will complete each week a menu and health tracker (Supplementary File 5), in which they will register their food consumption, medications, and symptoms. Before the study commencement, participants will be instructed to only consume the meals provided by the study team and they will be encouraged to do so during weekly visits. Regardless, the tracker provides a space to indicate unlisted food items that will have been consumed in addition to the formulated diet. Compliance will be determined by calculating the number (and proportion) of food items consumed that were provided and those consumed in addition. Participants who cannot comply to ≥90% of the feeding protocol will be excluded from the study. Participants will also be asked to record any medications (including over the counter medications) that were taken during the study period to account for any changes in inflammation. Participants will be asked to avoid if possible, taking any anti-inflammatory medications, and use acetaminophen instead if able. Regarding gastrointestinal tolerance, participants will complete a gastrointestinal tolerance questionnaire at the beginning and end of the study, to evaluate the effect of the diet on the GI system.

#### Anthropometric measures, body composition, and blood pressure

2.9.2.

Anthropometric measurements including weight, height, waist, and hip circumference will be assessed in duplicate according to standardized procedures (73, 74). Body weight will be measured to the nearest 0.1 kg using a calibrated digital scale (Health o meter^®^ Professional Remote Display, Sunbeam Products Inc., Fla., United States). Body weight will be recorded every other day at food pick-ups throughout the feeding period. Height is measured to the nearest 0.1 cm using a 235 Heightronic Digital Stadiometer (Quick Medical, North Bend, Wash., United States). Waist and hip circumference are measured to the nearest 0.1 cm, using a measuring tape (Hoechstmass^®^, Sulbzbach, Hesse, Germany).

Body composition is assessed once during the study by dual-energy X-ray absorptiometry (DXA) using a General Electric Lunar iDXA with encore 13.60 software (General Electric Company, Madison, Wis., United States), as described (75). This scan provides compartmentalized and whole-body data on fat mass (FM), lean soft tissue (LST), and bone mineral content (BMC). The coefficients of variation of this device for FM (%), FM (g), LST (g), and BMC (g) are 1.05, 0.99, 0.37, and 0.40%, respectively. The assessment is performed by a certified technologist. All females at premenopausal who are not using contraceptive methods will perform a rapid urine human chorionic gonadotropin immunoassay to confirm non-pregnant status before scanning.

Systolic and diastolic blood pressures will be measured in the left arm after a 10 min rest in the sitting position using a calibrated automatic blood pressure monitor (Spot Vital Signs^®^, Welch Allyn^®^, Skaneateles Falls, NY, United States).

#### Physical activity and habitual diet

2.9.3.

Participants will be required to maintain their current physical activity levels throughout the study period. They will complete the self-administered International Physical Activity Questionnaire (IPAQ) – Short Form, at baseline and post-intervention. The IPAQ inquires about time spent sitting, walking (3.3 METs), and doing moderate (4.0 METs) and vigorous-intensity (8.0 METs) activities over the past seven consecutive days. All continuous scores are expressed in MET-minutes/week and used to categorize physical activity level as low, moderate, or high. The IPAQ is a reliable questionnaire, and it has been validated in different settings across multiple countries (76).

Habitual dietary intake will be assessed at baseline using the Diet History Questionnaire III (DHQIII) (77, 78). The DHQIII is a validated food frequency questionnaire and will be administered to participants before the start of the study to estimate their habitual dietary intake of the past 4 weeks. We have selected the option to inquire about the food intake of the previous month to minimize recall bias as compared to covering the previous year.

#### Fasting blood collection

2.9.4.

Blood will be sampled from participants by venipuncture at five time points, after a 9–12 h overnight fast, by a trained phlebotomist. Blood sample is collected into BD Vacutainer^®^ tubes (Becton, Dickinson and Company, Franklin Lakes, NJ, United States), with spray-coated lithium heparin and a polymer gel or spray-coated K_2_-EDTA for plasma separation.

At the screening visit (Visit 1), blood samples (~ 8.5 mL) will be sent to the Alberta Precision Labs (Edmonton, AB, Canada) immediately after collection and are analyzed for HbA1c (4 mL K_2_-EDTA tube) or fasting glucose, triglycerides, total cholesterol, and HDL-c (4.5 mL lithium heparin tube). These analyses will be repeated at the baseline visit in case it is more than 2 weeks apart from the screening visit.

At baseline (visit 2 and 3) and final visits (visit 4 and 5), one K_2_-EDTA tube (~ 4 mL) will be analyzed for complete blood count and differential and HbA1c, and one lithium heparin tube (~ 4.5 mL) will be analyzed for glucose, insulin, lipid panel, and CRP in two consecutive days, to preclude an ongoing infection (i.e., CRP >10 mg/L), by Alberta Precision Labs (as above). Four K_2_EDTA tubes (~ 24 mL) will be analyzed in-house. Samples are kept at 4°C until being centrifuged at 1811 g for 10 min at 22°C. Plasma will be aliquoted for storage at -80^o^ C for subsequent analysis. The remaining buffy coat (leukocytes and platelets) and erythrocytes are resuspended with 3 mL of 1% bovine serum albumin (BSA, Sigma-Aldrich, Co., St. Louis, MO, United States) in phosphate-buffered saline (PBS) and layered onto Ficoll-Paque (HISTOPAQUE^®^-1,077, Sigma-Aldrich, as above), then centrifuged at 1558 g for 30 min with no brake at 20°C for PBMC isolation using density centrifugation. The lymphocyte band at the gradient interface of 1% BSA in PBS and Ficoll-Paque is transferred to a 50 mL conical tube, brought to 30 mL with 1% BSA in PBS, and centrifuged at 478 g for 5 min at 4 ^o^ C to pellet PBMCs. Supernatant is discarded and PBMCs are then washed with 10 mL 1% BSA in PBS and centrifuged as previously. PBMCs are resuspended in a cryopreservation solution containing Roswell Park Memorial Institute (RPMI) 1,640 medium (Thermo Fisher Scientific, Waltham, MA, United States) supplemented with 20% (v/v) fetal calf serum (FCS, Thermo Fisher Scientific, Waltham, MA, United States), 25 mmoL/L 4-(2-hydroxyethyl)-1-piperazineethanesulfonic acid (HEPES, Corning, Manassas, VA, United States), 2.5 μmol/L 2-mercaptoethanol (Thermo Fisher Scientific, Grand Island, NY, United States), and 1% (v/v) antibiotic/antimycotic solution (AB/AM, Sigma-Aldrich, as above) with 10% (v/v) dimethyl sulfoxide (DMSO, MP Biomedicals, Solon, OH, United States) added before use. PBMCs are then aliquoted to count using the trypan blue (diluted 1:1 with ddH_2_O, Corning, as above) membrane dye exclusion method using a 1:1 ratio of cell suspension to trypan blue. The remaining cell suspension is transferred to cryovials in 1 mL aliquots and immediately frozen at -80^o^ C using a freezing container ([name]™ Cryo 1°C, Nalgene^®^, Rochester, NY, United States). PBMCs are transferred to liquid nitrogen the next day for long-term storage. The RBC fraction is washed with 5 mL 0.9% saline and centrifuged at 453 g for 5 min at 4°C. Supernatant is discarded and RBCs are washed and centrifuged as previously. RBCs are lysed by bringing to 3 mL with double-distilled water (ddH_2_O), then stored at -80^o^ C for subsequent lipid analysis.

#### Oral glucose tolerance test

2.9.5.

The OGTT will be conducted once at the end of the feeding protocol. After a 9–12 h fast, an intravenous (IV) catheter will be inserted into a forearm vein for blood sampling by an experienced licensed practical nurse. After the IV catheter will be inserted, it will be flushed with saline before the first collection, and following each blood draw to ensure patency and rinse blood out of the catheter. Prior to each blood draw, a discard tube will be filled to a volume of at least 2 mL to clear the saline of the IV line. Blood samples will be collected into BD Vacutainer^®^ tubes (Becton, Dickinson and Company, as above), with spray-coated K_2_-EDTA for plasma separation. After the first blood collection (time 0), participants will be given up to 5 min to drink a beverage (296 mL) containing 75 g of dextrose (Trutol^®^ Glucose Tolerance Test Beverage). Then, blood samples will be taken every 30 min (±5 min) up to 180 min. For each time-point, ~ 6 mL of blood will be drawn. The IV site will be regularly monitored for phlebitis according to the Visual Infusion Phlebitis Score. During the test, participants will be allowed to drink water *ad libitum*. Plasma separation and PBMC isolation will be carried as described for fasting samples.

#### Stool collection

2.9.6.

Fecal samples are collected by participants at home or on-site before the start of the study diet and at the end of the study. The collection kit, which includes a collection device (FecesCatcher, TAG HEMI) and a fecal collection tube (DNA/RNA Shield™, Zymo Research Corp, United States) will be provided in a sealed plastic bag along with the instructions for proper handling of samples. Fecal samples will be kept at room temperature until brought to the research unit and will be stored at -80^o^ C for subsequent analysis.

#### Biochemical analysis

2.9.7.

##### Cardiometabolic risk factors/ systemic inflammation

2.9.7.1.

Biochemical analysis performed by Alberta Precision Labs includes (1) enzymatic colorimetric assays for triglycerides, total cholesterol, and HDL-C; (2) UV testing using an enzymatic reference method with hexokinase to quantity glucose; (3) an immunoturbidimetric assay for quantification of CRP, all using an automated photometric analyzer (Roche Cobas c503); (4) an electrochemiluminescence immunoassay to determine insulin using an automated immunology analyzer (Roche Cobas e801); and (5) a turbidimetric inhibition immunoassay for hemolyzed whole blood to determine HbA1c using an analyzer designed specifically for HbA1c quantification (Roche Cobas c513). Low-density lipoprotein-cholesterol (LDL-C) is calculated using the following equation: Totalcholesterol−HDLc−(Triglycerides÷2.2). Non-HDL-C is derived from the calculation of total cholesterol minus HDL-C. The Homeostatic Model Assessment for Insulin Resistance (HOMA-IR) index will be calculated using the equation: fasting insulin (microU/L) × fasting glucose (nmol/L)/22.5 (79).

Fasting and post-OGTT levels of circulating cytokines, chemokines, and soluble adhesion molecules will be measured using multiplex assay kits according to the instructions of the manufacturer. All samples will be run in batches with all timepoints per participant on the same plate to minimize variation. Post-OGTT plasma glucose will be measured using a clinical chemistry analyzer (Abbott ARCHITECT c4000, Canon Medical Systems Corporation, Otawara, Tochigi, Japan). The machine is calibrated and compared to controls based off manufacturer recommendations with a CV <5%.

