#### Recruitment

2.5.1.

The trial will recruit males and females from the Edmonton Metropolitan Region via the traditional media (newspaper, radio, and TV), word of mouth, institutional websites, social media advertisements, and posters placed on notice boards at the University of Alberta, obesity clinics, and other facilities from the surrounding area of Edmonton. A website and social media accounts (Instagram and Facebook) with the study information were also developed to support recruitment.^1^ Individuals can be included in the study if they meet all inclusion criteria and no exclusion criteria. All participants will be matched by age and sex, if possible, and participants with obesity will be matched for BMI and/or waist circumference. All females in reproductive stage which are not using contraceptive methods will be tested during the same follicular phase of their menstrual cycle (day 2 to 9), to account for immunometabolic changes, considering 4 weeks the mean duration of a menstrual cycle (62, 63). Participants will be allocated to one of four groups according to specific criteria for BMI, waist circumference, blood pressure, fasting glucose, hemoglobin A1c (HbA1c), triglycerides, and high-density lipoprotein-cholesterol (HDL-C) (Table 1). The cut off points used to identify obesity, cardiometabolic risk factors, and T2D were based on the World Health Organization (64), National Cholesterol Education Program-Adults Treatment Panel III criteria for metabolic syndrome (65) and Diabetes Canada (66), respectively.

**Table 1 tab1:** Eligibility criteria per group of adults.

Criteria	Lean-NG	Obese-NG	Obese-GI	Obese-T2D
BMI (kg/m^2^)	18.5–24.9 (±0.5)	≥ 30 (±0.5)		
Waist circumference (cm)	Males <102; Females <88	Males ≥102; Females ≥88		
Fasting blood glucose (mmol/L)^a^	<5.6		5.6–6.9	≥ 7.0
HbA1c (%)	<5.5		5.5–6.4	≥ 6.5^b^
BP (SBP/DBP, mmHg)	<130/85		NR	
Triglycerides (mmol/L)	<1.7		NR	
HDL-C (mmol/L)	Males ≥1.03; Females ≥1.29		NR	

BMI, body mass index; BP, blood pressure; DBP, diastolic blood pressure; HbA1c, glycated hemoglobin; HDL-C, high density lipoprotein-cholesterol; NR, not required in it that could be normal or elevated; SBP, systolic blood pressure; T2D, type 2 diabetes.

a If participants are at the upper or lower limits for fasting glucose, HbA1c will be used for group allocation.

b Or diagnosis of type 2 diabetes and use of medication.

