### Statistical analysis

2.10.

Continuous variables characterizing each study group will be reported as means with standard deviations or medians with interquartile ranges. Categorical variables will be represented as frequencies and proportions. Data will be checked for normality using the Shapiro–Wilk test, and logarithmic transformation will be employed for variables not normally distributed. The main comparisons in this study will be (1) between groups at each time point using analysis of variance with groups as the main effect followed by a multiple-comparison *post hoc* test and (2) within groups using paired *T*-test to assess differences between time points (i.e., baseline vs. post-intervention). Correlation analysis and linear regression models will be performed to verify the associations between outcomes (e.g., immune cell phenotypes and function, and systemic inflammation) and exposure (e.g., dietary intake or metabolic parameters, such as glucose, insulin, HOMA-IR, and HbA1c) variables. Mixed model repeated measures will be used to analyze variables of the OGTT to assess the effects of time, group, and time*group interaction. Overall comparisons of postprandial responses among groups will be determined using the incremental AUC with the trapezoid method. The statistical analyses will be adjusted for potential confounders and their interaction with the main group effect in cases where groups are unbalanced regarding factors such as physical activity level, use of medication (e.g., anti-diabetic drugs), and BMI, sex, and age if groups are not matched as initially planned. Sensitivity analyses will be conducted to verify the effect sizes of the primary outcomes of the study to assess the power and validity of our results. Comparative analyses using pertinent variables (e.g., age, sex, diet, metabolic profile, primary outcomes) will be performed between participants that completed the study with those who did not (i.e., participant dropouts or discontinuers). A *p*-value <0.05 will be considered to be statistically significant. A detailed analysis plan will be developed before the final analysis with a biostatistician.

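### The HOMA-IR equation carries the wrong units, and fasting insulin and HOMA-IR are used as exposures in insulin-treated participants, in whom they do not measure the participant's own insulin

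*Protocol article*

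**What the plan says.** Section 2.9.7.1 (Cardiometabolic risk factors/systemic inflammation) states that HOMA-IR will be calculated as "fasting insulin (microU/L) × fasting glucose (nmol/L)/22.5". It measures insulin by "an electrochemiluminescence immunoassay to determine insulin using an automated immunology analyzer". It mentions no C-peptide and places no restriction on whose HOMA-IR is calculated. Table 1 in section 2.5.1 gives glucose in a different unit: "Fasting blood glucose (mmol/L").

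Four other places decide who is affected:

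- Table 1, footnote b, on the HbA1c criterion for Obese-T2D: "Or diagnosis of type 2 diabetes and use of medication".
- Section 2.5.3 (Exclusion criteria). The only criterion that touches diabetes treatment is "participants under titration of their medication or initiating a new treatment or HbA1c >10.5"%.
- Section 2.7.1 (Concomitant care): "Participants should continue to take their regular medications", with examples that include "and glucose-lowering (metformin, insulin").
- Section 2.10 (Statistical analysis). The correlation and regression models relate immune phenotype, immune function and systemic inflammation to dietary intake or to "metabolic parameters, such as glucose, insulin, HOMA-IR, and HbA1c".

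Section 2.10 also plans to log-transform variables that are not normally distributed, and to adjust for anti-diabetic drugs and other factors where the groups are unbalanced.

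**The concern.** There are two defects, with different consequences.

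The first is that the printed units do not fit the constant 22.5 and do not match the glucose unit used for group allocation. Anyone who programs the equation as written, or compares reported values with other work, will be misled.

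The second is one of measurement. HOMA-IR is meant to describe the relation between a person's own fasting insulin and fasting glucose. In someone who injects insulin, an immunoassay reads the injected insulin to some degree or does not read it. In neither case is the result the quantity that the index needs. These participants all fall in Obese-T2D, so the error is concentrated in one group rather than spread evenly over the sample. At stake are the secondary associations of immune outcomes with fasting insulin and HOMA-IR, in a study that sets out to separate the contribution of obesity from that of glycemia.

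**Working it through.** **1. Units.** Inputs are the printed equation (section 2.9.7.1) and the Table 1 glucose cut-offs of 5.6 and 7.0 mmol/L. An insulin of 10 microU/mL is assumed for illustration.

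Conversions: 1 microU/mL = 10^3 microU/L, and 1 mmol/L = 10^6 nmol/L. The inflation is therefore 10^3 × 10^6 = 10^9.

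| Glucose (mmol/L) | microU/mL and mmol/L | Units as printed |
|---|---|---|
| 5.6 | 10 × 5.6 / 22.5 = 2.49 | 10^4 × 5.6×10^6 / 22.5 = 2.49×10^9 |
| 7.0 | 10 × 7.0 / 22.5 = 3.11 | 10^4 × 7.0×10^6 / 22.5 = 3.11×10^9 |

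The article states no HOMA-IR value, so there is no figure of its own to reproduce.

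**2. Does the factor matter for inference?** Multiplying an exposure by a constant c divides its slope by c and leaves r and p unchanged. On the log scale it adds ln c to every value, which moves only the intercept. A simulated data set with n = 128 confirms this: r = -0.254 and p = 0.0039 both with and without the factor 10^9, and the log-scale slope stays at -0.436 (p = 0.0036).

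**3. Who is affected?** Footnote b admits treated type 2 diabetes. The exclusion list removes titration, new treatment and HbA1c above 10.5%, but not stable insulin use. Section 2.7.1 keeps insulin going. Section 2.9.7.1 computes the index for everyone, and section 2.10 enters it as an exposure. Nothing in this chain excepts insulin users.

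The number of users is not given. Assuming 5–30% of 32: 0.05 × 32 = 1.6 and 0.30 × 32 = 9.6, so about 2–10 people. That is 1.6/128 = 1.3% to 9.6/128 = 7.5% of the sample.

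**4. How far could the association move?** If the assay returns k times the participant's own insulin, log HOMA-IR shifts by ln k for that person only. Three hypothetical readings:

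- k = 2.5: shift ln 2.5 = +0.92.
- k = 6.7: shift ln 6.7 = +1.90. This k is the ratio of two invented readings at glucose 9 mmol/L: 40 × 9/22.5 = 16.0 against 6 × 9/22.5 = 2.4.
- k = 1/3: shift ln(1/3) = -1.10.

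A simulation with n = 128, assumed group means and a true log-log slope of -0.4 gave this loss of slope for 2, 6 and 10 insulin users:

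| Assay reading | 2 users | 6 users | 10 users |
|---|---|---|---|
| 2.5-fold too high | 4% | 10% | 15% |
| 6.7-fold too high | 11% | 26% | 35% |
| Two-thirds too low | 1–4% across the three counts | | |

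If HOMA-IR were left untransformed, two users inflated 6.7-fold would cut the slope by about 69%. Leaving insulin users out recovered the log-scale slope in every case. All of these inputs are assumptions. The results show which factors drive the size and do not predict it for this trial.

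**The case against.** The strongest reply is that this is a condensed article, that section 2.10 promises a detailed analysis plan, and that the evaluability of a derived index in a treated subgroup is ordinary analysis-plan content. That has force: an analysis plan may already settle it. The article is not simply silent, however. It fixes an unrestricted calculation and names both variables as exposures, so following it as written mismeasures the exposure in these participants. The conditional adjustment for anti-diabetic drugs treats medication as a confounder. It may account for a difference linked to treatment, but it does not restore a mismeasured exposure.

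Other parts of the reply stand. HOMA-IR is one of four example exposures in secondary association analyses. No stated hypothesis names it, and it plays no part in group allocation. A sensitivity analysis without insulin users would also be a defensible way to handle them.

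A reader might infer more than the documents support:

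- *That the factor 10^9 invalidates the regressions.* It does not, because it is constant.
- *That HOMA-IR is invalid across the diabetic group.* The problem reaches only insulin users. Participants who are untreated or on metformin alone do not share it.
- *That insulin users necessarily have high leverage.* If the assay misses injected insulin, the illustrative value of 2.4 is an ordinary one, and log transformation softens the other case.
- *That a roughly 7-fold uncertainty describes this trial.* It contrasts two hypothetical assay behaviours. The article does not say how its assay responds to injected insulin.

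**Conclusion.** The point holds in two parts of unequal weight. The unit error is certain and should be corrected, but it is editorial: reported values and raw coefficients change and inference does not. The insulin-user problem is a real measurement error in two named exposures. It is confined to an unstated number of Obese-T2D participants and to the secondary association models for fasting insulin and HOMA-IR. Under the assumed scenarios, the log-scale distortion runs from about 1% to 35% of the slope, depending on assay behaviour, the number of users and the transformation. The conclusion rests on stable insulin users actually being enrolled, which the criteria allow but do not guarantee. The glucose and HbA1c models do not share the defect, and neither do the primary outcomes (CRP and IL-2) or the between-group and within-group comparisons of them.

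**What to change.** 1. In section 2.9.7.1, change the units to microU/mL (equivalently mU/L) for insulin and mmol/L for glucose, keeping the divisor 22.5.
2. In the detailed analysis plan, before the final analysis, state that fasting insulin and HOMA-IR are not evaluable in insulin-treated participants, and run the models with those two exposures without them. Add a sensitivity analysis that includes them, and report how many there are.
3. Keep all participants in the glucose and HbA1c models, so that the diabetic end of the range stays represented.

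The cost is one corrected line and a short addition to the analysis plan. The insulin and HOMA-IR models lose a small part of the sample at the diabetic end (about 2–10 people under the assumed range) and cover a treated subgroup less fully. No study procedure or treatment changes.
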